### 16.2.2 Model of Trachoma and Infection Elimination

We will simulate trachoma transmission using a stochastic (random process) model, where individuals are assumed to be repeatedly infected. We chose a stochastic modeling framework because chance effects are more important when we near elimination, and because experience with previous studies suggests considerable intercommunity variability which cannot be explained by other known indicators such as baseline prevalence, socioeconomic indicators, or antibiotic coverage. The model focuses on the core group of pre-school children, known to have the highest risk for and to carry the highest burden of infection. We assume that each child is either susceptible (not infected), or infectious, leading to a standard SIS model of transmission. We denote the number of infected children at any given time by  $Y$ , and the total number at risk by  $N$ . When a mass antibiotic administration occurs, a fraction  $c$  are covered with an antibiotic of efficacy  $f$ , and each infected individual has a probability  $\phi$  of being cured (and susceptible again). Between mass treatments, we assume that susceptible individuals become infected at a rate  $(\beta Y/N)$  proportional to the prevalence fraction  $Y/N$  of infection in the population. Once infected, individuals recover due to natural processes (even in the absence of antibiotic) at a constant rate  $\gamma$ , and again become fully susceptible once. These assumptions yield a standard continuous-time Markov process (with constant rates) which models the number of infected individuals until the next mass antibiotic administration occurs.

To estimate the site-specific transmission parameters for the stochastic model from epidemiological data, we use previously described methods. Briefly, we apply kernel-density estimators to simulation results to estimate a likelihood function from site-specific data collected

 Bailey N, 1957. The Mathematical Theory of Epidemics. London: Griffin

 Bartlett MS, 1956. Deterministic and Stochastic Models for Re-current Epidemics. Berkeley, CA: Proceedings of the Third Berkeley Symposium on Mathematical Statistics and Probability 4: 81–110.

before and after treatment. We maximize this likelihood, yielding both parameter estimates and their associated confidence intervals. Sensitivity and uncertainty analyses will be conducted on all parameters. Additional extensions to the model will include predicting the blinding sequelae of trachoma. All simulations and calculations will be conducted using *Mathematica* 6.0 (Champaign, IL).

This objective will proceed in several stages. In the first year of the project, we will construct the model given existing, pre-proposal data from each of the three study areas and from data available from other regions. Next, we will use the baseline and 6-month results of the antibiotic trial in this proposal to estimate site-specific parameters. We will validate the models using subsequent data from each of the sites in subsequent years. In years 4 and 5 of the proposal, we will use the models to estimate optimal treatment strategies, determining the most cost-effective coverage, frequency, and duration of treatment necessary to achieve elimination in 90% of communities.

Sensitivity analysis will be conducted based on varying the recovery rate parameter and repeating the simulations to ensure consistency (as we have done previously).

Additional extensions to the model will include within-community, household level heterogeneity. Transmission of infection may vary considerably even within pockets of a community, and these may be the same pockets that are most difficult to reach with antibiotic coverage. The longitudinal cohort studies in each of the three countries will provide the data necessary to assess the importance of heterogeneity and to adequately characterize it for inclusion in the model.

We can also use existing data to translate our conclusions about the prevalence of infection into what would be expected in terms of its consequences, clinical trachoma and trichiasis, the measures used by the WHO and trachoma programs.

### 16.2.3 Re-emergence: Longitudinal Study of Cohorts of Children

In each of the treatment arms there will be communities where all children aged 0-9 years will be followed overtime. To identify factors associated with presence active disease/infection in children, the following regression model will be used:

$$\text{Log} \frac{\Pr(Y_{it} = 1)}{\Pr(Y_{it} = 0)} = \alpha_0 + \beta_1 x_{1i}t + \beta_2 x_{2i}t + \beta_{12} x_{1i}x_{2i}t + \beta_3 t + \gamma_{it}$$

Where  $Y_{it}$  is an indicator variable for presence of trachoma/infection for child  $i$  at time  $t$ ,  $x_{1i}$ ,  $x_{2i}$ ,  $\beta_1$ ,  $\beta_2$ ,  $\beta_{12}$  have interpretations similar to the ones depicted in the previous longitudinal community level models,  $\beta_3$  describes the effect of time for the  $x_{1i}=0$  and  $x_{2i}=0$  group, and  $\gamma$  the effect of personal risk factors. In this model the effects of interest are quantified by  $\beta_1$ ,  $\beta_2$ ,  $\beta_{12}$  and correspond to different rates of change due to treatments. To account for the within-person serial correlation, standard errors will be corrected using the Generalized Estimation Equation approach. However, in these models, we can account for number of rounds of mass treatment experienced by the child, as well as the community, and model.

These cohorts also permit us to determine risk factors for re-emergence of infection or trachoma in children who at a previous round were free of either one and thus at risk. We will determine the risk associated with re-emergence as a function of number of previous rounds of mass treatment, and investigate the magnitude of infection/disease re-emergent clustering by family or neighborhood.

#### 16.2.4 Specific Analyses for the Niger site

The following analyses are planned for the Niger site (UCSF). All tests are two-sided with an alpha level of 0.05.

- In the annual azithromycin arm, we propose to compare resistance levels in pneumococcus from nasopharyngeal swabs taken at baseline to resistance levels at 36 months, to determine whether or not resistance levels have risen. This will be conducted using the Wilcoxon signed rank test on the differences (thus accounting for pairing). In all uses of linear regression or linear models with prevalence as the outcome, we propose to use the square root or fourth root transformation to stabilize the variance.
- In the biannual children arm, we propose the same analysis. Specifically, we propose to compare resistance levels in pneumococcus from nasopharyngeal swabs taken at baseline to resistance levels at 36 months, to determine whether or not resistance levels have risen. This will be conducted using the Wilcoxon signed rank test on the differences (thus accounting for pairing).
- At 36 months, we propose to compare the resistance levels in pneumococcus from nasopharyngeal swabs between two arms: the annual arm and the children biannual arm. We wish to determine whether or not treating children biannually causes more resistance than treating everyone annually. We propose to use the Wilcoxon rank sum test (there is no pairing).
- We propose to compare the chlamydia infection levels (from PCR taken from conjunctival swabs) in adults at baseline to the infection levels in adults at 36 months, in communities in the biannually treated arms. Because only children are treated, changes in adult prevalence are attributable to herd protection. The primary comparison will disregard the intended coverage target assignments and compare all villages using the Wilcoxon signed rank test (one-sample test on the differences, thus accounting for pairing). Supplemental analyses will (a) be conducted separately on the 90+% coverage arm, and (b) be conducted using a linear model with the outcome variable being the 36 month adult prevalence, and predictors being the baseline prevalence in adults, and coverage. Baseline prevalence in children may also be used as a predictor instead of baseline prevalence in adults.
- We propose to compare chlamydia infection levels in adults (based on PCR taken from conjunctival swabs) at 36 months between the adult mass treatment arms and the children treated arms. The intent is to compare the herd effect (seen in the children treatment arms) with the direct effect. Specifically, we propose to use a linear model with 36 month adult prevalence as the outcome, baseline adult prevalence, and coverage as predictors.
- We propose to examine the final prevalence (36 month) prevalence in children in a linear model for all study arms. We will look at high vs low coverage, and biannual-

child vs annual-all age indicators as predictors (a factorial model). Baseline prevalence will be used as a covariate.

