#### **4.3.1 Details on Randomization for Niger**

Figure 1 illustrates the sampling plan for Niger. We will be working in the Matameye department of the Zinder Region. We will randomize at the grappe level.

For randomization, we stratified based on geography and endemicity. As indicated above, we began with six CSIs. Each of these six CSIs contributed 8 grappes to the study—with two grappes per CSI allocated to each of the 4 arms (for a total of twelve grappes in each of four arms, or 48 total). Moreover, we ranked the eight grappes from each CSI by clinical activity in 0-5 year old children. The top four of these were considered higher prevalence, and the lower four were considered lower prevalence. When randomizing, one higher prevalence grappe from each CSI was randomized to each treatment arm, and one lower prevalence grappe was randomized to each treatment arm. Finally, each study arm has one randomly chosen grappe intended for detailed longitudinal follow-up.

Each of the 48 grappes will have a complete census; the census will be used to randomly select children as well as provide the basis for data on treatment according to randomization into treatment arm. After the census, we will have a complete listing of all children five years or younger. One hundred of these children will be randomly selected, by assigning each child a random number and choosing the children 0-5 years associated with the lowest 100 numbers (or all children if a grappe has less than 100 in this age group). A second group of 20 children will be randomly selected as a substitution group if not all children from the first group of 100 are available. If a child on the list of 100 is not examined, the reason will be recorded (anticipated reasons include: moved to nearby grappe, moved to Maradi, Zinder, or Nigeria, absent for the day, absent more than 1 month, sick, or guardian refused). In addition, 40 adults (age 15+) will be randomly selected for monitoring at each collection.

[figure not shown]

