### 5.3.1 Niger

#### 5.3.1.1 BACKGROUND

In Niger, all procedures and protocols must be approved by the National Ethics Committee. The National Ethics Committee has requested oral consent for all participants, following a standard protocol within the grappes. This study involves a random selection of children and adults, who will be screened for clinical trachoma and have a swab taken of the upper eye lid to determine presence of infection. In addition, a random sample of children will receive nasopharyngeal swabbing to test for pneumococcal resistance. All persons in participating grappes will have the opportunity to be treated according to their community's treatment assignment. Grappes not included in one of the study arms will still be offered treatment through the national treatment program.

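### The between-arm test of pneumococcal resistance in Niger ignores baseline resistance that the plan already uses, and gives no estimate of how large an excess remains possible

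*Protocol*

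**What the plan says.** Protocol 16.2.4 sets out three analyses of pneumococcal resistance from nasopharyngeal swabs, under the general rule "All tests are two-sided with an alpha level of 0.05".

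- **Within the annual arm, and again within the biannual-child arm:** baseline is compared with 36 months "to determine whether or not resistance levels have risen", by the Wilcoxon signed rank test on the differences.
- **Between the two arms at 36 months:** the aim is "We wish to determine whether or not treating children biannually causes more resistance than treating everyone annually", and the method is the Wilcoxon rank sum test. The reason given for that choice is that there is no pairing.

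The first bullet adds that any linear model with prevalence as the outcome will use a square-root or fourth-root transformation. The fifth and sixth bullets compare 36-month infection between the same arms, in adults and in children, by linear models that include baseline prevalence.

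On numbers, Protocol 4.3.1 allocates grappes "for a total of twelve grappes in each of four arms, or 48 total", so each frequency level has 24 when the coverage cells are pooled. For resistance, 5.3.1.1 says only that "a random sample of children will receive nasopharyngeal swabbing to test for pneumococcal resistance". The number of grappes or children swabbed is not given.

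**The concern.** The between-arm comparison addresses a possible harm of treating children twice as often: six rounds against three (Protocol Table 1). It is the only between-arm analysis of resistance in the document.

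Two features are weak. First, the baseline swabs exist in both arms and enter the within-arm tests, yet the between-arm test drops them. It is true that the arms are not paired with each other, but that is no reason to leave out a covariate measured on the same communities. Second, a rank sum p-value alone does not say how large an excess is compatible with the data. If the result is non-significant, a reader who wants to know whether six-monthly treatment is acceptable on resistance learns little.

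**Working it through.** **1. The plan's own figure.** The protocol gives no sample size or power for resistance. The nearest figure is for infection in Protocol 4.4.1: 11.9 communities per arm for 80% power at a 6-point difference, SD 5 points, two-sided 0.05. The protocol's formula is the non-central t with 2n − 2 degrees of freedom and non-centrality (δ/σ)√(n/2). At n = 12 this is 1.2 × √6 = 2.94, and power is 80.2%. Solving for 80% gives n = 11.94, so the stated figure reproduces.

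**2. Inputs for resistance.**
- Two-sided alpha 0.05 (16.2.4).
- Grappes per arm: 24 if the coverage cells are pooled (4.3.1). The comparison of the annual arm with the biannual-child arm reads most naturally that way. As the number swabbed is not stated, 12 is shown as a lower case.
- True difference 0.5 SD of community resistance: an assumption; the protocol gives neither an SD nor a relevant rise.
- Baseline to 36-month correlation 0.5: stated in 4.4.1 for infection, borrowed here.

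**3. Unadjusted test.** The t-test gives a reference value. The rank sum power was simulated with normal data.
- 24 v 24: non-centrality 0.5 × √12 = 1.73; t-test 40%, rank sum about 38%.
- 12 v 12: non-centrality 0.5 × √6 = 1.22; t-test 22%, rank sum about 19%.

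**4. Adjusted for baseline.** The residual variance is multiplied by 1 − 0.5² = 0.75 and the SD by √0.75 = 0.866. The standardised difference becomes 0.5/0.866 = 0.577.
- 24 v 24: non-centrality 0.577 × √12 = 2.00; simulated power about 49%.
- 12 v 12: non-centrality 0.577 × √6 = 1.41; simulated power about 25%.

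Repeat simulations move these figures by about one percentage point.

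**5. What an interval would show.** The unadjusted 95% half-width is t × √(2/n): 2.01 × √(2/24) = 0.58 SD at 24 v 24, and 0.85 SD at 12 v 12. Multiplying by 0.866 gives about 0.50 and 0.73 SD after adjustment. So even an observed difference of exactly zero at 24 v 24 leaves an excess of about half an SD open. For the within-arm change the half-width is 0.42 SD of the differences with 24 grappes and 0.64 with 12.

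**6. Sensitivity.**
- *Effect size:* at 1 SD, rank sum power is 91% at 24 v 24 and 60% at 12 v 12.
- *Correlation (24 v 24, 0.5 SD):* at 0.3 the non-centrality is 0.5/√0.91 × √12 = 1.82 and adjusted power about 42%; at 0.7 it is 0.5/√0.51 × √12 = 2.43 and about 65%. At zero correlation adjustment gains essentially nothing.

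**The case against.** The case for leaving the text alone is substantial. Resistance is an additional analysis, not a primary outcome or a stated research question, and the trial was sized for infection. Allocation was randomised within health-centre areas and prevalence strata, so the unadjusted rank sum test is valid. Adjustment is a matter of efficiency and does not turn a low-powered comparison into a well-powered one. All of this stands.

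Three stronger readings are tempting, and the documents do not support them.

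- **That a null test will be reported as resistance not having risen.** A reader might infer this from the whether-or-not wording, with a p-value as the only tool. No section says so, and the phrase is ordinary language for a hypothesis test.
- **That the tests miss a relevant rise in 37% to 81% of cases.** That range can be obtained by joining the signed rank test at 24 grappes to the rank sum test at 12 v 12. It mixes two different questions, rests on a half-SD rise that the protocol never states, uses a borrowed correlation, and needs 12 v 12 at its upper end. At 1 SD with 24 grappes per arm the misses are 9% or less.
- **That the plan is wrong for lack of a non-inferiority margin.** The protocol gives no basis for choosing one, and a margin for an additional outcome is detail that may be settled elsewhere. At 24 v 24, power to exclude a 0.5-SD excess when the true difference is zero would be only about 40%.

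What the objection does not answer is the choice that the protocol fixes: a between-arm test that omits an available baseline and yields no estimate, beside parallel infection analyses that include it.

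**Conclusion.** The concern holds as a point about precision and reporting, not as an error of validity. Under a 0.5-SD difference and a correlation of 0.5, adjustment raises power from about 38% to 49% at 24 v 24, and from about 19% to 25% at 12 v 12. Both assumptions come from outside the resistance text. The gain is larger if resistance is more strongly correlated over time and disappears if it is not correlated. A large difference would usually be found by either method at 24 v 24. An interval matters more than the gain in power, because at this size moderate excesses will often remain neither shown nor excluded, and a p-value alone hides that.

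**What to change.** In the third bullet of Protocol 16.2.4, replace the rank sum test with a linear model of 36-month community resistance on frequency arm, with baseline community resistance as covariate, on the square-root scale that the section already allows. A permutation test of the same adjusted statistic, with its interval obtained by inverting the test, would serve equally well.

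Report the adjusted between-arm difference and the two within-arm changes with 95% confidence intervals. Because a difference of square roots has no direct reading in percentage points, give back-transformed values or show the raw percentage-point difference alongside.

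Add one sentence: a non-significant result will not be read as showing no rise or no excess resistance.

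The cost is wording and a small amount of programming. It uses the baseline and 36-month swabs already planned and leaves the sample size unchanged. The price is that the report may have to call the comparison inconclusive.

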### 3.1 Niger

Historically, Niger has been hyperendemic for trachoma. Most individuals in the country received oral azithromycin in the mid 2000s, but the program has lapsed over the last 3 years. There is evidence that clinical trachoma has returned in some areas since the last treatment. The prevalence of clinically active trachoma in Matameye district has been estimated, and the Programme National de Lutte Contre la Cécité (PNLCC) and Carter Center have determined that retreatment is warranted. Previous data suggest at least three rounds of mass treatment will be necessary.

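### Niger adult analyses (16.2.4): an uncontrolled before-after change is declared herd protection, and the model for the randomised adult comparison lists no treatment-arm term

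*Protocol*

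**What the plan says.** Both items stand in protocol section 16.2.4, which sits under the heading for additional analyses and sets a general rule: "All tests are two-sided with an alpha level of 0.05".

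- **Change in untreated adults.** Adult *C. trachomatis* infection by PCR is compared between baseline and 36 months in the six-monthly, child-only arms. The protocol then says: "Because only children are treated, changes in adult prevalence are attributable to herd protection". On the test it says: "The primary comparison will disregard the intended coverage target assignments and compare all villages using the Wilcoxon signed rank test". The supplemental analyses (the high-coverage arm alone; a linear model on baseline prevalence and coverage) stay within the same arms.
- **Adults between arms.** Adult infection at 36 months is to be compared between the arms that treat everyone and those that treat children. "The intent is to compare the herd effect (seen in the children treatment arms) with the direct effect". The model follows: "Specifically, we propose to use a linear model with 36 month adult prevalence as the outcome, baseline adult prevalence, and coverage as predictors".
- **Children between arms.** The next item, on prevalence in children, begins its predictors "We will look at high vs low coverage, and biannual" and goes on to the child-only versus all-age arm indicator, calling this a factorial model.

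Section 4.3.1 supplies the data: twelve grappes in each of four arms, and "In addition, 40 adults (age 15+) will be randomly selected for monitoring at each collection".

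**The concern.** Section 1.1 lists among the trial's objectives whether six-monthly treatment of children can reduce infection in the whole community, that is, whether children are a core group for transmission. Section 8.2.1 builds the child-only arms on that idea, and the adult swabs are the data that bear on it most directly.

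Leaving adults untreated removes a direct drug effect as an explanation for change. It does not remove other explanations, and the protocol describes two:

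- **Baseline is not a steady state.** Section 3.1 reports mass treatment in the mid 2000s, then a lapse of three years, and adds: "There is evidence that clinical trachoma has returned in some areas since the last treatment".
- **The surroundings are treated.** Section 5.3.1.1 says that grappes outside the study arms are still offered treatment through the national programme. Less infection brought in from neighbours could lower adult prevalence whatever is done for children inside the grappe.

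The between-arm item has a different fault. It states a randomised contrast and then specifies a model that cannot estimate it. Followed literally, one analysis presupposes its conclusion and the other returns no estimate of its target.

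**Working it through.** **1. The plan's own figure.** The protocol gives no power, effect size or expected prevalence for the adult analyses, so there is nothing to reproduce for them. The nearest Niger figure is in section 4.4.1, hypothesis 2, on children: 12 communities per arm, difference 6%, SD 5%, two-tailed alpha 0.05, power above 80%. The non-central t with 22 degrees of freedom and non-centrality 6/(5 × √(2/12)) = 2.94 gives power 0.802. It reproduces and is not in dispute.

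**2. What the before-after test measures.** In the child-only arms (2 × 12 = 24 grappes) the expected change is the herd effect plus the background change. One sample of differences cannot split the two. With adult baseline prevalence of 10%, no herd effect and a background ratio of 0.75, the expected fall is 10% − 7.5% = 2.5 points, all of it background.

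Outside treatment could be extensive: section 4.3 gives 235 grappes in the area with 48 selected, leaving 235 − 48 = 187 outside the trial.

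**3. How often a false conclusion would follow.** A simulation used 1,000 runs per setting, 24 child-only and 24 whole-community grappes, and 40 adults per grappe at each time. Herd effect and arm difference were zero, and both arms had the same background ratio.

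- From the protocol: numbers of grappes and adults; two-sided alpha 0.05; correlation 0.5 between baseline and 36 months (section 4.4.1, stated there for the village sample size).
- Assumed: adult baseline prevalence 3% to 15%; lognormal village prevalence with CV 0.6; background ratio 1.0 to 0.35. The lowest ratio is 7%/20%, the Gambian decline in section 3.3. That is clinical disease at ages 1 to 9 over ten years, so it serves only as an outer illustration.

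Share of runs in which the planned signed-rank test rejects:

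| Adult baseline | Ratio 1.0 | 0.75 | 0.5 | 0.35 |
|---|---|---|---|---|
| 3% | 0.066 | 0.171 | 0.463 | 0.778 |
| 5% | 0.040 | 0.178 | 0.678 | 0.931 |
| 10% | 0.049 | 0.257 | 0.866 | 0.995 |
| 15% | 0.049 | 0.363 | 0.946 | 0.999 |

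With a ratio below 1, every rejection was a decline, which the attribution sentence would label herd protection. With no background change the test keeps roughly its nominal size.

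**4. The between-arm model.** As listed:

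Y36 = b0 + b1 × baseline adult prevalence + b2 × coverage

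Coverage cannot stand for the arm. Table 1 crosses coverage with frequency, and the child item names the two separately. The contrast that the item announces needs a further term:

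Y36 = b0 + b1 × baseline adult prevalence + b2 × coverage + b3 × arm

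In the same simulations, on square-root prevalence, the test of b3 rejected in 0.033 to 0.059 of runs over all sixteen settings, so a background change common to both arms does not disturb it. In one illustrative setting (baseline 10%; 36-month ratio 0.9 in child-only arms and 0.4 in whole-community arms) b3 was detected in 88% of runs.

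**The case against.** **The missing term is a drafting slip.** Very likely. The item's opening sentence names the two sets of arms, its predictors match those of the preceding within-arm supplemental model, where no arm term was possible, and the next item has the indicator. A reader might infer that the authors chose not to estimate the randomised contrast; the text does not support that. Stated aim and stated model still conflict, and the protocol fixes the predictors here instead of deferring them.

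**An untreated control was not available.** This stands as a limit of the design. Section 15.3, on a Tanzanian ancillary study, says that villages meeting trachoma criteria could not be randomised to no azithromycin. It limits what the before-after test can show and does not license the causal sentence.

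**The rival explanations are uneven.** This stands in part.

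- The reported return of trachoma points to a possible rise, which would mask herd protection. A reader might infer that every secular change would be counted as protection. Although the sentence speaks of changes in general and the test is two-sided, a rise would hardly be read that way.
- A reader might also blame regression to the mean, because section 5.1 admits communities with TF/TI above 10.5%. That selection is on a clinical sign, while the outcome is PCR infection in adults, so this is a weak rival.
- National treatment of neighbouring grappes is documented and works in the direction of a fall.

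**The rejection rates are not estimates for this trial.** Correct. They rest on assumed adult prevalence, spread and background change, and show direction and sensitivity only.

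**The completed arm comparison does not isolate herd protection.** Correct. Children are treated in both sets of arms, frequency differs as well as who is treated, and no arm is untreated. Higher adult prevalence in the child-only arms would be compatible with substantial herd protection or with none.

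**Conclusion.** The point holds for the wording of two items. First, the attribution sentence is wrong as written: the signed-rank test on 24 grappes cannot distinguish herd protection from background change in either direction. With no herd effect, a background fall of a quarter would give a false positive in 17% to 36% of runs, and a fall by half in 46% to 95%, under the assumptions listed. The size depends on those assumptions; the inability to separate the two causes does not. Second, the between-arm adult model has no coefficient for the contrast that it is meant to test, which follows from the listed predictors alone.

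A reader might go further and make the randomised adult comparison the main herd analysis, or conclude that the trial's main results are in doubt. The documents support neither. The comparison is of two strategies, and the change in untreated adults remains the more direct description of what happens to people who were not treated. Section 16.1 and the sample size rest on the sentinel children and are untouched. The changes should be made, at the weight of additional site-specific analyses.

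**What to change.** In section 16.2.4:

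1. In the between-arm adult model, add an indicator for six-monthly child-only versus yearly whole-community treatment, alongside the randomised coverage arm and baseline adult prevalence. Report the adjusted difference at 36 months with its confidence interval, described as a randomised comparison of strategies and not as an isolated herd effect.
2. Keep the signed-rank test as a description of change in untreated adults.
3. Replace the attribution sentence with wording such as: *A fall in adult infection in these arms would be consistent with herd protection but cannot be separated from secular trend, including the effect of national treatment in surrounding grappes.*

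The cost is a few lines of text. No new data, visits or swabs are needed, and the sample size does not change.
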